**Fig. 3 Fig3:**
[figure not shown]
Flowchart of the algorithm for the eight-step cerebral oxygen intervention

The assessment of postoperative cognitive function, another important finding of this study, has important clinical implications for investigating the potential mechanism of " *PHC → improves cerebral oxygenation → improves postoperative cognition. "* In this trial, the occurrence of DNR is quantified by scoring using the MMSE scale. However, we need to be clear that if, in the final statistical analysis, we find that the cognitive status between the two groups is not statistically different, or if there is a statistical difference, there is a cognitive-related confounding factor such as ASA grade or age. This outcome is possible and acceptable because this trial is not originally designed to explore the quantitative relationship between hypercapnia and postoperative cognitive performance. Although previous clinical evidence for the association between intraoperative rSO_2_ and cognitive function supports the potential hypothesis of "*PHC → improves cerebral oxygenation → improves postoperative cognition*," as shown in Table 5, researchers have not determined whether the specific mechanism of action is a simple effect of rSO_2_ or a combination of rSO_2_, cerebral oxygen metabolism, brain injury, neuronal apoptosis, and neurotransmitter regulation. In conclusion, both basic studies and large-scale risk factor analyses controlling for other possible confounders of postoperative cognitive function are inadequate, and the specific mechanism of the effect of cerebral oxygen saturation on postoperative cognitive performance is likewise not supported by sufficient evidence.

**Table 5 Tab5:** Summary of studies related to the association between rSO_2_ and postoperative cognitive function

Author	Year	Subjects	N	Oximeter	Outcomes
Trafidlo et al. [81]	2015	Lumbar spondylosis	43	INVOS 5100	NIRS cerebral oximetry may be helpful in reducing postoperative cognitive complications in patients operated on in the prone position
Murniece et al. [82]	2019	Spinal neurosurgery	34	INVOS 4100	The NIRS-based clinical algorithm may help avoid POCD in patients after spinal surgery
Casati et al. [83]	2005	Major abdominal surgery	122	INVOS 4100	A higher rSO_2_ improved MMSE scores in elderly patients undergoing major abdominal surgery
Slater et al. [84]	2009	Coronary artery bypass grafting	240	INVOS 5100B™	Intraoperative cerebral oxygen desaturation is significantly associated with an increased risk of cognitive decline
Colak et al. [85]	2015	Coronary artery bypass surgery	200	INVOS 5100c	Intraoperative cerebral oxygen saturation monitoring is beneficial for postoperative cognitive function outcomes, and rSO_2_ desaturation predicts POCD

In the future, based on the general direction of this study, we must strengthen the basic research on the effect of PHC on rSO_2_, clarify the specific mechanism, and further promote the popularization of the clinical application of NIRS. Basic research should be combined with evidence from multicenter, large-sample clinical trials to prove the strong association between PHC and rSO_2_. On the other hand, we should extend the hypothesis of "PHC-rSO_2_↑" to the postoperative cognitive function of patients and explore whether rSO_2_ is a beneficial factor for postoperative cognitive performance by performing RCTs or observational cohort studies with larger sample sizes.

Moreover, much more research is needed to explore the effects of PHC on cerebral oxygenation and postoperative cognitive performance, and several questions remain to be answered, as described below.①As a highly metabolic and oxygen-consuming organ, the brain has its own complex hemodynamic regulatory mechanisms, and the effect of PHC on it will likely vary substantially under different pathophysiological conditions. The pathophysiological states that might best benefit and the suitable and contraindicated populations must be determined according to the mechanism of action of PHC, which is the ultimate significance of basic research on PHC and the prerequisite for its clinical application.②After clarifying the beneficiary population, we must further develop a unified, standard processing specification, which we call the "*When/How (velocity* + *extent)/Duration*" algorithm: When should PHC be started? How can PHC standards be achieved? (in what way, at what speed, and to what extent) How long should PHC be maintained?③Having identified the applicable population and established the treatment criteria; we must further clarify the clinical safety and efficacy bounds of PHC. Based on the evidence from previous studies, the skylight effect of PHC on animal tests has been validated, and a reasonable range has been initially tested [6, 86], but all these parameters remain unclear in the clinical setting.

Only when the abovementioned issues are fully validated and solved can we genuinely apply PHC in the clinical setting and develop individualized protocols for specific patients, thus improving the significance of clinical practice and building a bridge between basic research and clinical application. In summary, the aging of the global population is gradually increasing, indicating that the number of older individuals requiring clinical and surgical treatment has increased simultaneously [87]. Moreover, this situation poses a significant challenge to healthcare institutions due to the unique characteristics of older individuals, such as declining physical functions, reduced reserve capacity of various tissues and organs, and degenerative changes in the central nervous system. Most previous studies on brain protection measures and related mechanisms are focused on basic research, while in clinical practice, they often explore measures in response to existing brain damage. Based on the predictability of NIRS technology, the current study monitors cerebral oxygenation to explore potential brain protection strategies, which have profound significance to the current world medical environment.

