In summary, when the three key factors of "older patients," "fragile brain function," and "CO_2_ pneumoperitoneum and laparoscopic surgery" are linked together, the protection of the perioperative cognitive function of patients must receive increasing attention. Notably, the change and adjustment of CO_2_ pneumoperitoneum pressure are extremely limited due to the essential requirement of a clear operative field for delicate surgical operations. However, it seems to be a pioneering prospect from the perspective of hypercapnia. First, although permissive hypercapnia was the intervention used in our study, in combination with clinical practice, mild hypercapnia itself is difficult to avoid in major laparoscopic surgery, and extreme ventilation parameter settings (high respiratory rate/high tidal volume) are often required to force normal conditions, which may exert adverse effects. Therefore, our intervention is different from that used in most other RCTs. We evaluated the advantages and disadvantages of both in terms of justifying their existence and acceptability in terms of medical factors, combined with the adverse effects (lung tissue traction injury, airway pressure damage, hyperventilation, respiratory muscle fatigue, tachycardia, etc.) of the forced manual setting of ventilation parameters to achieve a normal blood pH. Previous preclinical and clinical studies of the effects of hypercapnia on the central nervous system and postoperative cognitive function have largely produced negative results; however, further explorations are needed to determine whether this problem can be further improved when hypercapnia is converted to a more precise state of permissive hypercapnia.

Therefore, we will conduct a prospective, single-blind RCT. Laparoscopic colorectal surgery is used as the surgical method and older patients with NFBF are defined according to the "*Guidelines for the management of perioperative anesthesia in older patients in China*" [46], which are the main inclusion criteria used to explore our established hypothesis that the PHC group (H) will exhibit improved brain oxygenation and increased rSO_2_ compared with the target normal group (N) (Table 1). In addition, as a secondary objective, we will evaluate whether PHC affects postoperative cognitive outcomes and further verify the existence of the potential mechanism of "*PHC → improves cerebral oxygenation → improves postoperative cognition*."

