### Statistical analysis

Data will be analyzed using Statistical Package for Social Science 25.0 software. The Shapiro–Wilk test is used to test the normality of continuous variables, expressed as means and SDs if they are normally distributed and as medians and interquartile ranges if they are non-normally distributed. Baseline, Intraoperative, and postoperative indicators between the intervention and control groups are analyzed by t-tests, Mann–Whitney U test, chi-square test, continuous corrected chi-square test, or Fisher's exact test (Table 3). All primary and secondary outcomes analysis will be based on intention-to-treat (ITT) which means all patients who accept randomization will be included in the final statistical analysis, regardless of whether they received the intended intervention. We will also conduct per-protocol (PP) analysis for primary and secondary outcomes. ITT analysis usually attenuates differences between two groups, and PP analysis exaggerates differences between two groups. We will explore the consistency of ITT and PP analysis results and verify the results' reliability if they are consistent in the end. For the primary outcome, linear regression models will be used to generate unadjusted effect sizes with 95% confidence intervals. Preoperative baseline and intraoperative data are also included in the linear model to generate adjusted effect sizes and 95% confidence intervals. The analysis of repeated measures (rSO_2_, Da-jvO_2_, CERO_2_) will be performed using generalized estimating equations (GEE), with patient code (ID) as the within-subject variable, time as the between-subject variable, and rSO_2_, Da-jvO_2_, and CERO_2_ as the dependent variable. The ACE-R scores of the intervention and control groups will also be analyzed by GEE. What we need to be clear is that we will not adjust for multiple comparisons of secondary outcomes at numerous measurement time points, and we will focus on the separate effects of intervention because these results are exploratory. The incidence of CDE and DNR between the intervention and control group will be analyzed by the chi-square test, continuous corrected chi-square test, or Fisher's exact test. The serum NSE and IL-6 concentrations between the intervention and control groups are analyzed by covariance (ANCOVA) analysis, and the least-squares mean (LSM) difference and 95% CI will be estimated. Postoperative adverse events will be analyzed using the safety analysis set, which refers to patients who received at least one intervention in their group. Postoperative adverse events are categorical data, and the chi-square test, continuous corrected chi-square test, or Fisher's exact test will be used for statistical analysis.

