In addition, we will also perform statistical analyses (calculated using Fick's formula) of the relevant indicators of cerebral oxygen metabolism, "DajvO_2_ and CERO_2_" because the exploration of the potential correlation mechanism *"PHC → improves cerebral oxygenation → improves postoperative cognition"* is another critical objective of this study, and the significant correlation between cerebral oxygen metabolism and postoperative cognitive dysfunction has been confirmed [72, 73]. Although few previous studies related to PHC and cerebral oxygen metabolism have been conducted, studies on the relationship between the two have produced contradictory results, with evidence of positive, negative, and no correlations having been reported [12, 74–76]. However, we maintain that the final findings will support the hypothesis that PHC accompanied by a higher rSO_2_ improves cerebral oxygen metabolism and reduces the incidence of DNR, thus improving cognitive function outcomes. In addition, our analysis of serum NSE and IL-6 levels by collecting blood samples may reveal significant differences between the two groups. The intervention group may be able to mitigate perioperative brain injury through the multifaceted brain-protective mechanism of PHC, and NSE and IL-6 levels will be lower than those in the control group as predictors of brain injury.

According to the logical stratification of this study, we included postoperative cognitive outcome as a secondary outcome, and graded these parameters quantitatively based on MMSE scale scores to assess the postoperative cognitive function status of the two groups and combined with the differences in the effects of PHC interventions on "rSO_2_, DajvO_2_, CERO_2_, NSE, and IL-6 levels" in the two groups, a multifaceted and multilevel approach will be used to verify the proposed mechanism of *"PHC → improves cerebral oxygenation → improves postoperative cognition."*

Other secondary findings, including surgical prognosis, postoperative complications, the incidence of adverse effects, and length of hospital stay, lack relevant clinical evidence and theoretical support and require us to explore the intrinsic associations through the specific trial process.

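### The Discussion excuses in advance both a null cognitive result and a significant one accompanied by age or ASA grade, and the planned cognitive analyses contain no adjustment that would settle the matter

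*Protocol article*

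**What the plan says.** **Discussion, paragraph on postoperative cognitive function (after Fig. 3).** Two outcomes are described together. One is that "we find that the cognitive status between the two groups is not statistically different". The other is that "if there is a statistical difference, there is a cognitive-related confounding factor such as ASA grade or age. This outcome is possible and acceptable". The reason given is that "this trial is not originally designed to explore the quantitative relationship between hypercapnia and postoperative cognitive performance".

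**Background, final paragraph.** As a secondary objective, "we will evaluate whether PHC affects postoperative cognitive outcomes", and the same sentence extends this to verifying the chain from permissive hypercapnia (PHC) through cerebral oxygenation to cognition.

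**Anticipated results.** The authors write that "we maintain that the final findings will support the hypothesis that PHC accompanied by a higher rSO", and the sentence goes on to include a lower incidence of DNR. The section then says that the MMSE results, combined with the oxygenation and marker data, will be used to verify the mechanism.

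**Statistical analysis.** For DNR, "The incidence of CDE and DNR between the intervention and control group will be analyzed by the chi-square test", its continuity-corrected form or Fisher's exact test. For scores, "The ACE-R scores of the intervention and control groups will also be analyzed by GEE"; the ACE-R appears nowhere else in the article, and the scale chosen is the MMSE. Adjustment for baseline and intraoperative data is stated for the primary outcome's linear model, and ANCOVA for NSE and IL-6. No covariate is named for either cognitive analysis. Secondary results at the various time points are called exploratory.

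**The concern.** The article gives the cognitive data two incompatible roles. In the Background and Anticipated results they test and verify a mechanism. In the Discussion they come from a trial not built for the question, so a null is acceptable, and so is a difference that comes with an age or ASA explanation. The Discussion does not say how large an imbalance must be, which analysis would show that it matters, or whether the clause covers benefit, harm or both. That judgement is left until the results are known.

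In a randomised comparison, a baseline difference in age or ASA grade is chance imbalance. The sound way to deal with it is to name the covariates beforehand and read the adjusted estimate. Calling it confounding afterwards puts the interpretation in the hands of whoever has seen the data.

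Harm is a real possibility on the article's own account. The Background says that earlier work on hypercapnia and cognition was largely negative, and it describes mechanisms by which harm could arise.

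**Working it through.** **1. The readings side by side**

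| Cognitive result | What the Discussion provides | Effect on the hypothesis |
|---|---|---|
| No significant difference | Acceptable; trial not designed for this | Neither supports nor refutes |
| Significant benefit, with an age or ASA factor | Acceptable; explanation at hand | Support is weakened |
| Significant harm, with an age or ASA factor | Acceptable; explanation at hand | Contrary evidence can be set aside |
| Significant difference, no such factor | Not addressed | Open |

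The second and third rows need a criterion for when the factor explains the difference. None is given.

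**2. Arm size**

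The Sample size section gives 68 in total, raised for 10% loss: 68 / 0.9 = 75.6, so 76, or 38 per arm. This reproduces. (The 68 itself concerns rSO2 and no SD is stated. An assumed SD of 10 with a difference of 8 gives 33.8 per arm by t-test, so 34 per arm and 68 in total.) No figure is given for cognition, so all DNR rates below are assumptions.

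**3. What randomisation covers and what adjustment adds**

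Simulation: 4,000 trials, 38 per arm, no treatment effect, one prognostic covariate with an assumed log-odds of 0.8 per SD on a binary outcome.

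| | Unadjusted | Adjusted |
|---|---|---|
| Type I error, all trials | 5.4% | 4.9% |
| Trials with arms more than 0.4 SD apart (8%) | 9.1% | 4.4% |

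Overall error is already controlled. In the minority of trials with a marked imbalance the unadjusted test is too liberal, and pre-specified adjustment corrects it. So there is a real question about imbalance, and adjustment answers it.

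**4. What a DNR test can show with 38 per arm**

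Exact enumeration of two binomials, two-sided 5%:

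| Assumed rates | Power, uncorrected chi-square | Power, Fisher | Non-significant |
|---|---|---|---|
| 20% vs 40% (doubling) | 48.9% | 39.7% | 51% to 60% |
| 30% vs 15% (halving) | 34.9% | 26.3% | 65% to 74% |

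A null is therefore weak evidence either way. An interval says more than the p-value. For observed rates of 40% on PHC and 20% on control, the half-width is 1.96 × sqrt((0.4×0.6 + 0.2×0.8)/38) = 1.96 × 0.1026 = 0.201. The risk difference of 20 points then has an interval from about 0 to 40 points. That result sits at the edge of significance, yet it leaves almost no room for benefit.

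**5. MMSE: gain over a GEE without a baseline covariate**

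Assume a difference of 0.5 SD on the average of days 1, 3 and 7, 38 per arm, and an equal correlation ρ between all visits. Per-patient variance in SD² units:

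- Change-type contrast (post mean minus baseline): (1 + 2ρ)/3 + 1 − 2ρ
- Post mean adjusted for baseline: (1 + 2ρ)/3 − ρ²

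The standard error of the difference is sqrt(2 × variance / 38).

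| ρ | Change: variance, SE, power | Adjusted: variance, SE, power |
|---|---|---|
| 0.5 | 0.667, 0.187, 75% | 0.417, 0.148, about 92% |
| 0.6 | 0.533, 0.168, 84% | 0.373, 0.140, 94% |

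The article does not state the contrast that the GEE will use, so the change-type form is also an assumption.

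**The case against.** **The sentence is a caveat, not a decision rule.** It is one awkward Discussion sentence on an exploratory outcome. Its natural reading is conditional: it covers a difference that coexists with a cognition-related factor, and not every difference. This stands. A significant harm with balanced arms is not excused by the text.

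**A reader might infer that no cognitive result could count against the hypothesis.** The documents do not support that. Putting a significant benefit down to age or ASA weakens the hypothesis, and a difference without such a factor is not addressed. What follows is narrower: under the conditions described, the result neither confirms nor refutes.

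**A reader might also infer that the baseline comparisons are there to supply grounds for discounting.** The Statistical analysis section does say "Baseline, Intraoperative, and postoperative indicators between the intervention and control groups are analyzed by t-tests" and other tests, but nothing links those tests to the reading of cognitive results.

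**Treating a null as inconclusive is fair.** This stands, and the power figures above support the authors' caution.

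**Unadjusted tests are valid, and covariates for secondary outcomes may be left to an analysis plan.** Both statements are true in general. Here, however, the article itself states the unadjusted DNR method and itself raises age and ASA as possible explanations. Having named the problem, it should name the adjustment. The optimistic wording about results supporting the hypothesis appears as an expectation, but the claim to verify the mechanism does not fit with the Discussion's disclaimer.

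**Conclusion.** The point holds in a limited form. The Discussion accepts a null, and also a significant difference accompanied by age or ASA grade, without a criterion. The stated cognitive analyses give no pre-specified way to decide whether such a factor matters. As planned, the cognitive data cannot carry the verifying role given to them elsewhere, and a significant harm could be explained away afterwards.

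The gain from adjustment is moderate: error in markedly imbalanced trials (about 8% of them) falls from 9.1% to 4.4%, and MMSE power rises by roughly 10 to 17 percentage points against a change-type GEE. These sizes rest on an assumed prognostic strength, an assumed equal correlation of 0.5 to 0.6 and an assumed 0.5 SD effect. The DNR power figures rest on assumed rates. A null stays inconclusive at 38 per arm whatever is done. The primary rSO2 conclusion and the sample size are not touched.

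**What to change.** 1. **Discussion:** delete the clause that accepts a significant difference because of a factor such as age or ASA grade. State that the cognitive effect will be read, in either direction, from a pre-specified estimate with its 95% CI, and that an interval lying on the side of harm or excluding benefit counts against the hypothesis. Keep the statement that a null is inconclusive at this size.
2. **Statistical analysis, scores:** replace ACE-R with MMSE, and analyse the day 1, 3 and 7 scores by GEE with baseline MMSE, age and ASA grade as covariates.
3. **Statistical analysis, DNR:** report the risk difference with 95% CI, and an age- and ASA-adjusted estimate beside the chi-square or Fisher test.
4. **Anticipated results:** soften the statements that the findings will support the hypothesis and verify the mechanism, and align the Background's secondary objective with them.

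**Cost:** wording only. Age and ASA grade are listed in Table 3, and the MMSE is taken the day before surgery, so no data, patients or visits are added. The models use a few degrees of freedom, and the DNR model must stay small because events will be few.

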## Data Availability

Not applicable.

## Abbreviations

rSO_2_: Regional cerebral oxygen saturation
NIRS: Near-infrared spectrum
PHC: Permissive hypercapnia
NFBF: Nonacute fragile brain function
RCT: Randomized controlled trial
ASA: American Society of Anesthesiologists
BMI: Body mass index
TIA: Transient ischemic attack
AD: Alzheimer's disease
PD: Parkinson's disease
ARDS: Acute respiratory distress syndrome
PETCO_2_: End-tidal carbon dioxide tension
CDE: Cerebral oxygen desaturation events
MMSE: Mini-mental state examination
MoCA: Montreal Neurocognitive Assessment
CAM: Confusion Assessment Method
Da-jvO_2_: Difference in arteriovenous oxygen content
CERO_2_: Cerebral oxygen uptake rate
PNDs: Perioperative neurocognitive disorders
DNR: Delayed neurocognitive recovery
POD: Postoperative delirium
POCD: Postoperative cognitive dysfunction
ABG: Arterial blood gas
NSE: Neuron Specific Enolase
CSF: Cerebrospinal fluid
CBF: Cerebral blood flow
PACU: Postanesthesia care unit
PCIA: Patient-controlled intravenous analgesia
